**Figure 2 F2:**
[figure not shown]
**Oddvar Holten diagram**.

**Figure 3 F3:**
[figure not shown]
**Formula**. A: lifted weight; B: percentage of intensity.

ACSM recommends to not do a maximal aerobic exercise test in nonclinical settings during pregnancy [25]. During pregnancy maximal heart rate reserve decreases and resting heart rate increases. This makes the standard training HR formulas ineffective [25]. ACOG and Canadian guidelines therefore recommend the use of ratings of perceived exertion (RPE) in addition to heart rate [23,26]. Borg's conventional 6–20-point scale is recommended, with 12 to 14 (a rating of 13 corresponds to a subjective rating of "somewhat hard") identified as the RPE range to apply in pregnancy [27,28]. The PARmed-X form pregnancy document modified the target HR zones for exercise prescription from the suggested target HR zones for nonpregnant individuals. The target HR zone suggested for women aged 20–29 yr is 135–150 bpm and for women aged 30–39 yr 130–145 bpm [29]. These target HR zones during pregnancy represent approximately 60–80% of aerobic capacity based on age [23]. A check to avoid overexertion will be the "talk test". The exercise intensity is too high if the exercising pregnant woman is not able to carry on a verbal conversation [23,29]. Aerobic training will be executed on cycle ergometers, treadmills, cross-trainers, and when still possible with the pregnant belly, on stationary rowing machines. For every aerobic exercise a baseline level of intensity will be estimated. This prediction will be done as follows: for example a woman starts cycling at a low work rate of 50 watt with a pedal rate at 50 rpm. The physiotherapist increases the work load till an intensity is reached that equals a Borg scale rating of 12. Woman than maintain cycling for 10 minutes on that intensity. Exercises in the subsequent session will start on that baseline intensity. When the RPE is rated under 12, the intensity will be increased by increasing the working load. At each training, attendance and the intensity of all strength and aerobic exercises will be registered by the physiotherapist.

Training will take place under close supervision of a physiotherapist. The physiotherapists will have expertise with providing training for pregnant women. The physiotherapists will use the guide of the American College of Obstetricians and Gynaecologists [26,30] to maintain a safe and healthy exercise program. Warning signs to terminate exercise are; vaginal bleeding, dyspnoea before exertion, dizziness, headache, chest pain, muscle weakness, calf pain or swelling, preterm labour, decreased foetal movement, amniotic fluid leakage [26]. Furthermore, during training classes women will be encouraged to be physically active in their daily live also. Walking and cycling are activities that can be maintained up until delivery, and these are easily incorporated into daily live. To motivate the women for daily physical activity, information on the benefits for mother and child will be given at the start and during the intervention. If indicated, women in the intervention group will be treated as usual for GDM or other complications during pregnancy.

#### Control group

The control group will receive usual care given by obstetricians and midwives. Dutch midwives and obstetricians follow closely the health status of each pregnant woman and their unborn child. The first appointment is usually between 9^th ^and 12^th ^week of gestation. For women who develop GDM during the study, usual care consists of dietary advice and insulin treatment. Every treatment will be registered in the medical records.

#### Non-participants

Women who decide not to participate after reading the information brochure at home are asked to return a reply coupon. They are asked to fill in weeks of pregnancy, body weight, body height and reason for not participating. Characteristics of this group will be compared to those women who do participate in the study.

### Outcome measurements

Participants in both intervention and control group are invited for three measurement appointments during pregnancy and one appointment after pregnancy (see Table 1). Outcome measurements are assessed at baseline (around 15 weeks of pregnancy), 24 and 32 weeks of pregnancy and 12 weeks postpartum by means of physical measurements, laboratory tests, and self-administered questionnaires.

**Table 1 T1:** Schedule of measurements.

**T0: 15 weeks pregnancy**	**T1: 24 weeks pregnancy**	**T2: 32 weeks pregnancy**	**T3: 12 weeks post partum**
Fasting blood sample	OGTT*	OGTT	Fasting blood sample
	Ultrasound*	Ultrasound	Neonatal weight**
Maternal weight	Maternal weight	Maternal weight	Maternal weight
Accelerometer	Accelerometer	Accelerometer	Accelerometer
Questionnaire	Questionnaire	Questionnaire	Questionnaire

*measurement as part of usual care in hospital; **weight of the baby at delivery, as part of usual care.

*Primary maternal outcome *measures are fasting plasma glucose and relative increase in insulin resistance. *Primary neonatal outcome *is birth weight.

*Secondary outcome *measures are: maternal serum triglycerides, HDL, cholesterol and HbA1c, maternal weight gain during pregnancy, maternal physical activity level, foetal growth. Changes in direct health care and non-health care costs and indirect non-health care costs are studies as well.

Although the groups are too small to be able to detect statistically significant changes in these outcomes, the following variables will be assessed as well because of their clinical importance: incidence of gestational diabetes, macrosomia (97^th ^percentile for gestational age), and complications during pregnancy or delivery, such as preeclampsia, caesarean section rate and need for labour induction. These outcomes will be collected from the medical records of the gynaecologist or midwife.

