**Methods:**

The FitFor2-study is a randomised controlled trial. Women who visit one of the participating hospitals or midwifery practices and who are at risk for gestational diabetes are eligible to participate. After baseline measurement they are randomly allocated to in the intervention or control group. The intervention group receives an exercise program twice a week in addition to usual care. The exercise program consist of aerobic and strength exercises and takes place under close supervision of a physiotherapist. Data are collected at 15, 24 and 32 weeks of pregnancy and 12 weeks after delivery. Primary maternal outcome measures are fasting plasma glucose and relative increase in insulin resistance. Primary neonatal outcome is birth weight. Secondary outcome measures are: maternal serum triglycerides, HDL, cholesterol, HbA1c, maternal weight gain during pregnancy, maternal physical activity level, foetal growth.

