## Methods

### Study design

This study is designed as a randomised controlled trial (RCT), to assess whether an exercise program improves insulin sensitivity and fasting plasma glucose levels of women at high risk for gestational diabetes, assuming that this will lower their risk of GDM. The design is presented in Figure 1. The Medical Ethics Committee of VU University Medical Centre at Amsterdam has approved the study design, protocols, and informed consent procedure. All participants must provide a written informed consent. After baseline measurements, participants will be randomly allocated to the control or intervention group. The participants will be followed for 9 months: from 15 weeks of pregnancy until 12 weeks after delivery.

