### Inclusion and exclusion criteria

Pregnant women at increased risk for gestational diabetes will be eligible to enter the study when they meet the following inclusion criteria: between 14 and 20 weeks of pregnancy; over 18 years of age; sufficiently fluent in Dutch; being able to be moderately physically active; and willingness to give written informed consent.

Women will not be admitted to the RCT if they meet any of the following exclusion criteria: diagnosed with (gestational) diabetes mellitus before randomisation; hypertension (systolic pressure > 160 mmHg and/or diastolic pressure > 100 mmHg); alcohol abuse (i.e. 2 glasses alcohol or more per day); drug abuse (except for incidental analgesic agents); use of the medication that affects insulin secretion or insulin sensitivity (antiviral, corticosteroids, antihypertensive drugs, all concomitant medication will be discussed); serious pulmonary (COPD, exercise-induced asthma), cardiac, hepatic or renal (serum creatinine < 150 μmol/l) impairment; malignant disease; serious mental or physical impairment i.e. preventing to understand or implement the study protocol/aim.

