### Recruitment

Women will be recruited at the Departments of Obstetrics of VU University Medical Centre (VUMC), St. Lucas Andreas Hospital (SLAZ) and Onze Lieve Vrouwe Gasthuis (OLVG) in Amsterdam and 10 midwifery practices in Amsterdam. The obstetricians or midwives in the 3 hospitals and midwifery practices will introduce the study at the first visit of every pregnant woman who is eligible for inclusion. They will give the pregnant women who are interested to participate a brochure about the study to read at home. Obstetricians and midwives will also fill out a reply coupon (name, telephone number, inclusion and exclusion criteria) and will send this coupon to the research team. Interested women can return the informed consent form to the research team or the research team calls within two weeks after receiving the reply coupon. When women meet the inclusion criteria and want to participate, they will be included. After inclusion, an appointment for the baseline measurement will be made.

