### Intervention

#### Intervention Group

Participants randomised to the intervention group will complete an exercise program on two days of the week during the remaining duration of the pregnancy. Each session will last for 60 minutes. The exercise program will consist of aerobic and strength exercises that will help to control the blood glucose level. All sessions will be completed under the guidance and supervision of a specifically trained physiotherapist. The sessions will be located at the Department Physiotherapy of the participating hospitals (VUMC, OLVG and SLAZ).

At the first session the participants will be introduced to the exercise program. They will be informed about the structure of the sessions and will receive instructions in the use of the equipment. Each exercise session will begin with a warming-up for 5–10 minutes. This is a light intensity activity, such as slow cycling at a level of intensity of 50 Watt, that prepares the muscles for exercise. After the warming-up, each participant completes an individualised program of 40 minutes, consisting of 1 or 2 aerobic exercises and 4 to 6 strength exercises. After exercising, participants cool down for 5–10 minutes by slowly reducing the activity. This allows the heart rate to return to normal levels.

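### Maternal weight gain is measured from a baseline that can fall anywhere from 14 to 20 weeks up to week 32, so it covers unequal intervals and is not gain over the whole pregnancy

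*Protocol article*

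**What the plan says.** **Entry.** The protocol article, Inclusion and exclusion criteria, admits women "between 14 and 20 weeks of pregnancy". Under Recruitment it adds: "After inclusion, an appointment for the baseline measurement will be made".

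**Baseline.** Four places put T0 at or near week 15:
- The abstract: "Data are collected at 15, 24 and 32 weeks of pregnancy and 12 weeks after delivery".
- Study design, which counts follow-up "from 15 weeks of pregnancy until 12 weeks after delivery".
- Outcome measurements: "Outcome measurements are assessed at baseline (around 15 weeks of pregnancy), 24 and 32 weeks of pregnancy and 12 weeks postpartum".
- Table 1, whose column head gives no window: "T0: 15 weeks pregnancy".

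**Weighing and programme.** Table 1 schedules maternal weight at T0, at 24 weeks (T1), at 32 weeks (T2) and 12 weeks after delivery. The secondary outcome is named as the mother's weight gain in pregnancy, with no start or end week. The Intervention Group section has the exercise programme run "during the remaining duration of the pregnancy".

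**Analysis.** Statistical analysis describes longitudinal linear regression and keeps a confounder when it shifts the regression coefficient by 10% or more. The Questionnaire section gives an open list of candidate confounders, in which gestational age at baseline is not named.

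**The concern.** A woman included at 18 or 20 weeks cannot have a 15-week baseline, and around 15 does not reasonably stretch to 20. The entry window and the T0 label therefore disagree. Because the later visits are tied to gestational age, a late entrant has less time in which to gain weight between T0 and week 32, whichever arm she is in. Part of the spread in the outcome then reflects entry week.

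The name of the outcome raises a second issue. The schedule has no weight before T0 and none in pregnancy after week 32, so it cannot deliver gain over the whole pregnancy. A result for T0 to 32 weeks could be reported as if it covered the full period, with the last part of the programme unobserved.

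**Working it through.** **Inputs from the protocol article.** Entry at 14 to 20 weeks (Inclusion and exclusion criteria); T0 after inclusion (Recruitment); T1 at 24 and T2 at 32 weeks (Table 1); 64 women per arm after losses (Sample size).

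**Assumptions, not in the document.** Delivery at 40 weeks (range 37 to 42); gain of 0.3 to 0.5 kg per week; SD of gain 3 to 5 kg; entry uniform over the window, and T0 at the week of entry.

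**1. Interval = visit week minus T0 week.**

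| T0 week | to week 24 | to week 32 | to week 40 | share of T0 to week 40 covered by week 32 |
|---|---|---|---|---|
| 14 | 10 | 18 | 26 | 18/26 = 69% |
| 15 (as labelled) | 9 | 17 | 25 | 17/25 = 68% |
| 20 | 4 | 12 | 20 | 12/20 = 60% |

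The T0 to T2 interval varies 1.5-fold (18/12) and T0 to T1 varies 2.5-fold (10/4).

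**2. Unweighed time before delivery.** 40 − 32 = 8 weeks; 37 − 32 = 5 and 42 − 32 = 10 weeks at the ends of the range.

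**3. Added variance in weight gain.** The SD of a uniform entry week is (20 − 14)/√12 = 1.73 weeks. Multiplied by 0.3 to 0.5 kg per week, this is a nuisance SD of 0.52 to 0.87 kg. Relative increase in variance = (nuisance SD / SD of gain)²:
- smallest: (0.52/5)² = 0.27/25 = 1.1%
- largest: (0.87/3)² = 0.75/9 = 8.3%

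The SD itself rises by about 0.5% (√1.011) to 4% (√1.083). If entry in practice falls at 14 to 16 weeks, the SD of entry week is 2/√12 = 0.58 weeks and the variance rises by only 0.1% to 0.9%.

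**4. Chance difference between arms.** The standard error of the difference in mean entry week is 1.73 × √(2/64) = 0.31 weeks, or 0.09 to 0.15 kg at the assumed rates. This is random error centred on zero.

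**5. What the 10% rule does with it.** Adjusting for gestational age at T0 moves the treatment coefficient by roughly the amount in step 4. A typical shift of 0.09 to 0.15 kg reaches 10% of the coefficient only when that coefficient is below about 0.9 to 1.5 kg (0.09/0.10 to 0.15/0.10). Whether the covariate enters therefore depends on chance imbalance and on the size of the estimate, and not on how well it predicts gain.

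**6. Which outcomes are affected.**
- Maternal weight gain: yes, weight is taken at T0.
- Insulin resistance: not shown. The analytes listed for the fasting sample do not include insulin, both indices are described under the OGTT, and Table 1 has the OGTT only at 24 and 32 weeks. On that text the only increase clearly computable runs over 8 weeks in every woman.
- Foetal growth: no, ultrasound is at 24 and 32 weeks for all.
- Birth weight: no, taken at delivery.
- Fasting glucose: not defined as a change.

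**The case against.** The strongest defence is that the recruitment path leads to early baselines. The Control group section puts the first appointment usually at 9 to 12 weeks, the study is introduced at the first visit, and the team calls within two weeks of receiving the coupon. Twenty weeks may then be a ceiling and around 15 the target. This is plausible, and step 3 shows that the extra variance would nearly vanish. It does not remove the mismatch, since the text still admits entry up to week 20.

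It can also be said that visits tied to gestational age are sensible, because glucose results are then compared at the same gestation; that Table 1 openly shows the weighing weeks; and that covariates are commonly left to an analysis plan. The first stands, and nothing here asks for the visits to move. The second softens the labelling problem but does not correct the name. The third stands in part, but the article does state a selection rule, and step 5 shows that this rule does not reliably bring in gestational age at T0.

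Two stronger readings are tempting. A reader might infer that the comparison of arms is biased. It is not: T0 precedes allocation, so entry week is balanced in expectation, and chance imbalance is part of ordinary sampling error. A reader might also infer that the primary outcome on insulin resistance suffers from the same unequal intervals. The document does not show an insulin measurement at T0, so that cannot be concluded. Likewise, the gap of 6 × 0.3 to 0.5 = 1.8 to 3.0 kg between the earliest and latest entrants compares two extreme women, not the two arms.

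**Conclusion.** The point holds for one secondary outcome, and it is minor. The T0 label contradicts the entry window. Gain from T0 to 32 weeks covers 12 to 18 weeks depending on entry, and the name of the outcome claims more of the pregnancy than is measured. The interval figures follow directly from the document, taking T0 at the week of entry; a later booking would shorten them further. The unmeasured tail of about 8 weeks rests on an assumed delivery at 40 weeks. The 1% to 8% increase in variance rests on assumed uniform entry, rate of gain and SD of gain, and it is probably an upper picture if most women enter early. The harm is a little lost precision and a label that could mislead, without systematic bias in the treatment comparison.

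**What to change.** 1. Reconcile the T0 label with the entry window wherever it appears (abstract, Study design, Outcome measurements, Table 1), and record the exact gestational age at T0.
2. Define the secondary outcome as maternal weight gain from T0 to 32 weeks, and report it under that name.
3. Include gestational age at T0 as a prespecified fixed covariate for that outcome, outside the 10% change-in-coefficient rule. Do the same for any other outcome that is in fact measured as a change from T0.

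The cost is small. No visit or measurement is added, because gestational age has to be known to apply the entry criterion. The one real price is a narrower claim: the trial would speak about gain up to 32 weeks, not about the whole pregnancy.

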### Data collection

#### Physical measurements

##### • Maternal anthropometric measures

Maternal body weight gain will be measured by calibrated electronic scales (SECA 888) while participants are only wearing indoor clothing. Body weight will be measured twice, and the mean value of the two measurements will be computed.

Maternal body height will be measured on bare feet by a (wall mounted) height scale.

##### • Foetal and neonatal anthropometric measures

Foetal growth during the pregnancy will be measured by ultrasound. Obstetrical ultrasound will be used to assess the growth of the foetus. It will be performed by a sonographer of the hospital at 24 and 32 weeks of pregnancy.

Birth weight: At delivery, birth weight will routinely be measured and recorded by the obstetrician, midwife or the nurse. We will gather the birth weight from the medical records of the obstetrician of midwife.

##### • Physical activity

Physical activity will be measured by an accelerometer. At 15, 24 and 32 weeks of pregnancy and 12 weeks after delivery an accelerometer will be sent to all participants. They have to wear the accelerometer (Actitrainer) for 4 consecutive days to gather, objective data on the amount of daily physical activity.

#### Questionnaire

• Physical activity will be assessed with the Activity Questionnaire for Adolescents & Adults (AQUA) [31].

• Quality of life will be assessed with the EuroQol [32,33].

• All costs related to pregnancy and delivery: direct health care and non-health care costs and indirect non-health care costs. Examples of direct health care costs are costs for visits to the general practitioner, medical specialists, therapists, dieticians, costs of medication and hospitalisation. Examples of direct non-health care costs are the costs of over-the-counter medication, travel time, and waiting time. Indirect costs will include the costs of absence from paid and unpaid work. Costs will be calculated by multiplying the volume of resource use by cost prices, following the Dutch guidelines for economic evaluations in health care to estimate costs [34].

• Potential confounding variables such as age, ethnicity, socio-economic status, working status, and parity will be measured also.

#### Laboratory tests

##### • Fasting blood samples

Fasting blood will be drawn from the antecubital vein after a participant has fasted for at least 10 hours. From this blood samples glucose, HbA1c, HDL-cholesterol, triglycerides and cholesterol will be measured. HDL-cholesterol, triglycerides and cholesterol will be measured by means of enzymatic techniques (Boehringer-Mannheim, Mannheim, Germany). HbA1c will be measured by High Performance Liquid Chromatography. Plasma glucose will be measured in plasma by means of a hexokinase-method (Roche Diagnostics GmbH, Mannheim, Germany).

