##### • Oral Glucose Tolerance Test (OGTT)

An OGTT will be performed after a fasting period of at least 10 hours. Blood samples will be collected in the fasting state and 30, 60, 90, 120 and 180 minutes after ingestion of a glucose drink (100 g D-glucose in 0.5 l water). Participants should not eat anything or do any physical activity or exercise during the test. The insulin sensitivity index will be calculated from a 100-g OGTT according to the equation derived by Matsuda and DeFronzo [35] in which insulin sensitivity is estimated by using the fasting and mean glucose and insulin concentrations in serum and HOMA-index. Simple fasting method to measure insulin resistance is the homeostasis model assessment (HOMA) (= fasting insulin concentration (μU/mL) × fasting glucose concentration (mmol/L)/22.5)) [36].

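### As printed, the primary outcome of relative increase in insulin resistance has no baseline value: insulin is not listed for the T0 sample and no reference visit is named

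*Protocol article*

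**What the plan says.** Under Outcome measurements, the primary maternal outcomes "measures are fasting plasma glucose and relative increase in insulin resistance". No starting visit for the increase is given there or under Statistical analysis.

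The same section sets the visits: "Outcome measurements are assessed at baseline (around 15 weeks of pregnancy), 24 and 32 weeks of pregnancy and 12 weeks postpartum". The blood-test row of Table 1 reads, from T0 to T3, "Fasting blood sample OGTT* OGTT Fasting blood sample".

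Under Laboratory tests, the fasting-sample paragraph lists its analytes: "From this blood samples glucose, HbA1c, HDL-cholesterol, triglycerides and cholesterol will be measured". It then gives an assay method for each of these. The OGTT paragraph describes two insulin measures. For the first, "The insulin sensitivity index will be calculated from a 100-g OGTT", using glucose and insulin concentrations. The second is HOMA, fasting insulin times fasting glucose divided by 22.5, introduced with the words "Simple fasting method to measure insulin resistance is the homeostasis model assessment (HOMA". It is not tied to a visit.

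Under Study design, allocation follows baseline: "After baseline measurements, participants will be randomly allocated to the control or intervention group". The entry window is "between 14 and 20 weeks of pregnancy".

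**The concern.** A relative increase needs a starting value. In a randomised trial that value should precede allocation, so that treatment cannot have altered it. The printed visit table and assay list supply no such value for insulin resistance.

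An analyst who worked only from the listed measurements would be left with the change from 24 to 32 weeks. Both ends of that change are post-randomisation. An exercise effect that had appeared by 24 weeks would sit in the denominator and be divided out. The primary outcome could then show little or nothing although insulin resistance was lower in the exercise arm throughout. If the proportional effect shrank after 24 weeks, the ratio could even favour control.

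**Working it through.** The plan gives no figure for this outcome that could be reproduced; its power calculation concerns fasting glucose and birth weight. The check therefore sets visits against analytes, followed by short arithmetic.

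**1. Is insulin resistance available at each visit, as printed?**

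| Visit | Blood test (Table 1) | Insulin available? | HOMA or OGTT index |
|---|---|---|---|
| T0, 15 weeks | Fasting sample | Not in the assay list | Neither |
| T1, 24 weeks | OGTT | Required by the OGTT index | Both |
| T2, 32 weeks | OGTT | Required by the OGTT index | Both |
| T3, 12 weeks postpartum | Fasting sample | Not in the assay list | Neither |

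The only increase during pregnancy that these entries allow is T1 to T2.

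**2. How late is the T1 denominator, and how much of the period is covered?** For baseline at week w, T1 comes 24 − w weeks later, and T1 to T2 covers 8/(32 − w) of the time from baseline to T2.

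- w = 14: T1 is 10 weeks later; 8/18 = 44%
- w = 15: T1 is 9 weeks later; 8/17 = 47%
- w = 20: T1 is 4 weeks later; 8/12 = 67%

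**3. What does a T1-to-T2 ratio do to an effect?** Let control HOMA be C1 and C2 at T1 and T2, and let exercise lower it by proportions e1 and e2. The relative increase is C2/C1 under control and C2(1 − e2)/[C1(1 − e1)] under exercise. Exercise divided by control is

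(1 − e2)/(1 − e1).

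The control values cancel. The true effect at T2 is 1 − e2.

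The article gives no HOMA values, so those below are assumed:

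- *Constant effect, e1 = e2 = 20%.* Control goes from 2.0 to 3.0, and 3.0/2.0 = 1.5. Exercise goes from 1.6 to 2.4, and 2.4/1.6 = 1.5. The arms do not differ in relative increase, although the level is 20% lower at both visits.
- *Growing effect, e2 = 20% and e1 from 0 to 20%.* The ratio runs from 0.80/1.00 = 0.80 (nothing lost) to 0.80/0.80 = 1.00 (all lost). At e1 = 10% it is 0.80/0.90 = 0.89, an apparent reduction of 11% in place of 20%.
- *Shrinking effect, e1 > e2.* The ratio exceeds 1 and favours control.

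**4. What does a T0 denominator do?** With HOMA at T0 the denominator precedes allocation, so e = 0 there and the ratio at T2 is 1 − e2, which is the whole effect.

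**The case against.** The strongest reply is that the article has left something out and the design is sound. Much of this stands.

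- **The lists are visibly incomplete.** No insulin assay or method is listed for any visit, although the OGTT index plainly needs insulin at T1 and T2. A reader might infer that insulin is deliberately not measured at T0. The article does not say so; it only fails to list it.
- **A fasting baseline may have been intended.** HOMA is presented as a simple fasting method. At T1 and T2 the OGTT index is already available, so a fasting measure adds most at the fasting-only visits.
- **No 24-to-32-week ratio is planned.** A reader might take it to be the declared outcome. It is only what the listed measurements permit. It also suits the longitudinal regression poorly, because it yields one value per woman, whereas increases from T0 yield two.
- **The insulin question survives.** A reader might conclude that the trial cannot say whether exercise improves insulin sensitivity. That does not follow. Randomisation makes a comparison of levels at T1 and T2 valid without a baseline; in the constant-effect example it shows the 20% difference at both visits. Fasting glucose, the other maternal primary outcome, has a T0 value and is unaffected.

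What the reply does not remove is the mismatch on the page. A journal article may leave detail to the full protocol, but this one prints a specific assay list and a specific visit table, and together they cannot yield a named primary outcome from baseline. The longitudinal model cannot supply a T0 value that was never assayed.

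**Conclusion.** The point holds for the outcome as printed: the relative increase in insulin resistance has neither a pre-randomisation value nor a stated reference visit. That part rests on the text alone.

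The size of the consequence is conditional. If the increase were taken from T1 to T2, the loss would be complete under a constant proportional effect and partial under a growing one. The article has no data on how the effect develops, so the numerical examples illustrate a range and do not predict a result. If insulin is in fact assayed at T0, only the wording needs correcting.

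The point deserves attention because a primary outcome is involved and a baseline sample cannot be taken again once exercise has started. It does not show that the trial is unable to answer its insulin question.

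**What to change.** 1. Add fasting insulin to the assay list for the T0 sample, which is already being drawn.
2. State that the relative increase is in HOMA and is counted from T0. One way that keeps the planned longitudinal regression is to take log HOMA at T1 and T2 as the outcome, with log HOMA at T0 as covariate. The back-transformed group coefficient is then the ratio between arms of the relative increases from T0, adjusted for baseline.
3. Say that the OGTT index, which has no T0 value, is compared between arms as a level at T1 and T2.
4. Where T0 insulin cannot be recovered for women already enrolled, compare log HOMA or log OGTT-index levels at T1 and T2 between arms, and do not use the T1-to-T2 increase.

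The cost is about 160 insulin assays on existing samples and a change of wording, with no extra visit or blood draw. An insulin assay at T3 is optional, since the increase during pregnancy does not need it.
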